### **7.4 Summary of known and potential risks and benefits**

There are no known or expected risks related to the oral ingestion of the related sugars. By consuming these sugars twice in our trial, we can measure the gut permeability to assess the effect of the intervention product on gut permeability.

### **7.5 Description and justification of route of administration and dosage**

All sugars (4.5 gram in total per administration) will be dissolved in a single glass of water, which will be ingested orally on CID 1 and CID 3. This amount and way of ingestion is tested and proven reliable in previous studies.(39)

### **7.6 Dosages, dosage modifications and method of administration**

Two-step hyperinsulinemic-euglycemic clamp:

- Insulin and glucose 20% (clamp): i.v. glucose 20% strongly dependent on the insulin sensitivity of the participant.
- [6,6-2H2]-glucose (clamp): i.v. prime concentration of 2.4 mg/kg body weight and a continuous infusion of 0.04 mg/kg/min for t = -120 to 330 minutes. The infusion will be set at a concentration that has no metabolic effect in humans (tracer amounts).
- Lidocaine (AT and skeletal muscle biopsies): 4-6 ml for local subcutaneous injection.

Gut permeability:

- 1 gram lactulose, 1 gram sucralose, 1 gram erythritol, 0.5 gram rhamnose for each administration. All will be dissolved in water and administered orally. No dosage modification is needed.

### **7.7 Preparation and labelling of Non Investigational Medicinal Product**

Please find more detailed information in the attached documents D2.

All products used will be prepared in the kitchen or laboratories of the MRUM facilities.

Products to be used will be labelled as follows:

- Study name (DISTAL-study)
- Participant code
- Date and time of intake
- Expiration date

### **7.8 Drug accountability**

Not applicable

## **8. METHODS**

### **8.1 Study parameters/endpoints**

#### **8.1.1 Main study parameter/endpoint**

The main endpoint is the difference in change in peripheral muscle insulin between intervention and control group, measured by hyperinsulinemic-euglycemic clamp.

#### **8.1.2 Secondary study parameters/endpoints**

Difference in changes in pre- and posttreatment values between intervention and control group, regarding the following parameters/endpoints:

- Hepatic and adipose tissue insulin sensitivity
- Energy and substrate metabolism (energy harvest, intake, expenditure, carbohydrate and fat oxidation)
- Body weight, composition and body fat distribution (anthropometrics, DEXA)
- Plasma and faecal concentrations of butyrate, propionate and acetate (SCFA) and proteolytic substrates (BCFA, indoles, ammonia)
- Plasma concentrations of inflammatory markers (IL-6, TNF- $\alpha$ , IL-1), circulating metabolites (glucose, triglycerides, FFAs) and hormones (insulin, GLP1, PYY, glucagon) and blood lipid spectrum (total cholesterol, HDL, triglycerides/TAG)
- Brain health: food reward related brain activation and cognitive function (CANTAB, fMRI)
- Gut permeability
- Faecal microbiota composition and functionality (Metagenome and -transcriptome sequencing)
- Gastrointestinal side effects (GRGS / BSS)
- Expression of gene and protein expression in adipose and muscle tissue

#### **8.1.3 Other study parameters (if applicable)**

- Three day food record: completed before CID 1 and 3 and the visit in week 6.
- Physical activity questionnaire: completed before CID 1 and 3 and visit in week 6 (SQUASH)
- Questionnaires on general wellbeing and quality of life, (family) medical history, stress, sleeping habits and fatigue, mood, satiety

### **8.2 Randomisation, blinding and treatment allocation**

Participants will be randomized to the intervention or placebo group using a validated variable block randomization using Qminim. Furthermore, minimization will be used to ensure group comparability. Factors included for minimization are age, sex and BMI.(40) Initially, CASTOR

EDC would be used for randomization and stratification for this study. After the change from stratification to minimization, however, CASTOR cannot be used since it has no minimization option. Therefore, Qminim will be used, with which there is extensive experience within our research group.

Randomization and preparing and distribution of the, for participant and investigator, unrecognizable dietary supplement (either a potato-pectin fibre mixture or placebo) will be carried out by an independent researcher. This ensures that only the independent researcher knows which subject received which supplement, while both the participant and original investigator remain blinded to the treatment. In case of emergency, the independent investigator can debind the participant(s).

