### 3. STUDY DESIGN

The proposed study will be a double-blind, randomized placebo-controlled trial, to evaluate the effect of a potato-pectin fibre mixture on gut, metabolic, immune and brain health by optimizing saccharolytic and proteolytic fermentation. Individuals aged 30-75 years with overweight or obesity ( $\text{BMI} \geq 28 \text{ kg/m}^2 < 40 \text{ kg/m}^2$ ) and impaired fasting glucose (defined as fasting glucose 5.6-6.9 mmol/l or HbA1c 42-47 mmol/mol) or insulin resistance ( $\text{HOMA-IR} > 1.85$ ) will be included in the study.

All visits regarding this study will take place at the facilities of the department of human biology or the Metabolism Research Unit Maastricht of Maastricht University, or at the clinical facilities of Maastricht University Medical Center+.

After the application of an individual via (e-)mail or phone (see [Chapter 4](#) for recruitment), the researcher will contact the potential participant by email or phone to provide additional information regarding the study, answer questions and determine possible eligibility, after which a week of consideration will be given. After a week, the potential participant will be contacted again and, if they are still interested in participating, a screening visit will be planned.

The first visit to our facilities will consist of the following components:

- Checking an individual's wellbeing, medical history and determining eligibility and safety of participation.
- Signing informed consent
- Measuring vital parameters and body measurements (body weight, length, waist-to-hip ratio, systolic and diastolic blood pressure)
- Taking blood samples to determine eligibility based on specific inclusion criteria (20ml to determine glucose, insulin, ALAT, creatinine, HbA1c)

The participant will visit our facilities after a >10h overnight fasted state.

All eligible participants will be equally randomized over the two arms (potato-pectin fibre mixture vs placebo) with stratification for age, sex and HbA1c (see [Chapter 8.2](#)). The entire trial period after screening and randomization will take 13 weeks, which will be explained in more detail below.

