#### 4.4 Sample size calculation

We used G-power to calculate the sample size required to detect a clinically relevant change in peripheral insulin sensitivity.

To calculate the sample size, we used the data derived from previous clinical trials of our research group using a comparable participant population to assess effects of alterations of the gut microbiota on peripheral insulin sensitivity with the hyperinsulinemic-euglycemic clamp technique. Based on the studies' data we calculated a within-group residual SD of 2.70, which was based on a SD of post measurement of 3.95 and a pre-post correlation of 0.73;  $\sqrt{(1-0.732)} \times 3.95 = 2.70$ . Twenty-two (we aim to include an equal number of males and females: 11

males and 11 females) participants per group (N = 44) are needed to detect a physiological relevant difference of 20% (2.86µmol/kg/min) in the change in our primary outcome parameter peripheral insulin sensitivity measured via the hyperinsulinemic-euglycemic clamp technique, assuming a power of 80%, an  $\alpha$ -value of .05, a within-group residual SD of 2.70 and a 20% dropout rate. The described secondary outcomes will be analysed exploratively, for microbiome analysis Benjamini-Hochberg procedure will be used to prevent false-positive results.

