### 10.1 Primary study parameter(s)

We will be comparing the intervention group versus the placebo group regarding the change in insulin sensitivity as measured by the two-step hyperinsulinemic-euglycemic clamp. Changes in glucose disposal rate and infused glucose concentrations before and after the 12 week intervention period are our primary study parameters and will be analysed and compared between the two groups. Data from both groups will be analysed using a linear mixed model to include repeated measures. An intention-to-treat and per-protocol analysis will be conducted. Intervention and study period will be set as fixed factors, participants will be set as random factor. Age and sex will be added as covariates in the analysis.

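### Sections 3 and 8.2 give different allocation methods and factors, and the primary model omits the third allocation factor; the statistical cost is small

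*Protocol*

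**What the plan says.** Section 3 of the protocol has 1:1 allocation "with stratification for age, sex and HbA1c" and refers to chapter 8.2 for detail.

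Section 8.2 opens by assigning participants "using a validated variable block randomization using Qminim", then adds minimisation: "Factors included for minimization are age, sex and BMI". It also records that the method was changed: "After the change from stratification to minimization, however, CASTOR cannot be used since it has no minimization option".

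Section 10.1 specifies a linear mixed model: "Intervention and study period will be set as fixed factors, participants will be set as random factor". The covariate list is fixed there: "Age and sex will be added as covariates in the analysis". Neither BMI nor HbA1c appears, and no intervention-by-period interaction is named.

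**The concern.** Two things do not fit together. First, sections 3 and 8.2 are both current text, yet they differ in method (stratification or minimisation) and in the third factor (HbA1c or BMI). These two factors are not interchangeable: section 4.2 requires every participant to lie in the BMI range, whereas the HbA1c range is only one of three alternative entry criteria. Section 8.2 also does not say how variable blocks and minimisation would be combined.

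Second, an analysis should normally reflect the factors on which allocation was balanced. If a balanced factor predicts the outcome and is left out, its variance stays in the residual. The model-based standard error then overstates the true one, and the test can become conservative. In a trial of 44, that is precision the design has already provided.

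**Working it through.** **1. The texts side by side**

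| Place | Method | Factors |
|---|---|---|
| Section 3 | Stratified randomisation | age, sex, HbA1c |
| Section 8.2 | Variable blocks, then minimisation in Qminim | age, sex, BMI |
| Section 10.1 | Linear mixed model | age, sex |

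The omitted factor is HbA1c if section 3 governs and BMI if section 8.2 governs. One factor is omitted either way.

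**2. Inputs from section 4.4**

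- Follow-up SD 3.95, pre-post correlation 0.73. Residual SD = √(1 − 0.73²) × 3.95 = √0.4671 × 3.95 = 2.70, which reproduces the plan's figure. This is the SD of the follow-up value after adjustment for baseline.
- The SD of change, assuming equal SDs at both visits, would be 3.95 × √(2 × (1 − 0.73)) = 2.90.
- Difference 2.86 µmol/kg/min, two-sided 5%, 20% dropout: 44 × 0.8 = 35.2, so 35 completers.
- A two-sample t-test on these inputs needs 16 per arm, or 16/0.8 = 20 with dropout, so 40 in total. The planned 44 is somewhat larger; nothing below depends on this.

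**3. Cost of the omission in a baseline-adjusted analysis**

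The protocol gives no correlation between BMI and insulin sensitivity, so the partial correlation r is an assumption. In 4,000 simulated trials, 44 participants were minimised on median-split age, sex and BMI with a 0.85 biased coin (also assumed), and 35 completed at random. The residual SD was 2.70. The model contained age and sex, with or without BMI.

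| Assumed r | Type I error without BMI | with BMI | Power without BMI | with BMI |
|---|---|---|---|---|
| 0 | 4.9% | 4.9% | 83.6% | 82.4% |
| 0.2 | 4.5% | 4.6% | 84.6% | 85.0% |
| 0.3 | 4.2% | 4.4% | 84.3% | 86.9% |
| 0.4 | 4.3% | 4.8% | 85.2% | 89.4% |

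The changes in power from adding BMI are −1.2, +0.4, +2.6 and +4.2 points.

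A second simulation (8,000 trials, 0.8 coin) gave type I error without BMI of 5.1%, 4.9% and 4.4% at r = 0.2, 0.3 and 0.4. Adding BMI moved power from 83.8% to 82.8% at r = 0, from 83.8% to 84.1% at r = 0.2, and from 84.6% to 88.7% at r = 0.4. A further simulation with baseline adjustment gave type I error of about 4.4 to 4.6% and a gain of about 0 to 5 points over r = 0.2 to 0.4.

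Simulation error on a 5% rate is √(0.05 × 0.95/4000) = 0.34 points for 4,000 trials and 0.24 for 8,000, so small differences between these rates should not be over-read. Above the assumed range the cost grows: at r = 0.5 the first simulation gives 3.4% without BMI, and power of 85.9% without against 92.2% with it.

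**4. Cost of the omission in the two-visit mixed model**

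Write participant i's outcome at visit t as a random intercept, plus β × BMIᵢ, plus period and intervention-by-period terms, plus error. In the change from visit 1 to visit 2, β × BMIᵢ subtracts out. With complete data, the intervention-by-period contrast is the difference in mean change, so BMI as a main effect cannot alter it.

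A simulated dataset with 18 per arm and a prognostic BMI shows this: the contrast is 3.48 (SE 0.95) both with and without BMI. If instead no interaction is fitted and the intervention coefficient is read as the effect, it moves from 0.77 (SE 1.54) to 1.45 (SE 1.40) when BMI is added. The effect of the omission therefore depends on a contrast that section 10.1 does not name.

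**The case against.** The text conflict largely resolves itself. Section 3 defers to 8.2, and 8.2 records both the change of method and the change of software, so section 3 reads as a sentence that was not updated. This stands. A reader might infer that two rival allocation lists could be built; the protocol does not support that, because the operative section can be identified. What remains is a superseded method and factor in current text, and an unexplained mention of blocks in 8.2 itself.

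The stronger objection concerns the mechanism. Section 8.1.1 defines the endpoint as a between-group difference in change, so the natural reading of section 10.1 is the intervention-by-period contrast. There, BMI as a main effect drops out with complete data. This also stands: it cannot be said without qualification that the planned confidence intervals are too wide. It does not show the omission to be harmless, since section 10.1 names no interaction and section 4.4 sizes the trial with a baseline-adjusted SD.

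A reader might also apply the closed form for a perfectly balanced factor. SE inflation of 1/√(1 − r²) − 1 gives 2.1%, 4.8% and 9.1% at r = 0.2, 0.3 and 0.4, and type I error falls to 4.6%, 4.0% and 3.3%. These figures overstate the effect. Minimisation on categories of a continuous factor, followed by 20% dropout, does not give perfect balance, and none of the simulations reaches 3.3% at r = 0.4.

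Finally, covariates are often left to a statistical analysis plan. Here the protocol itself fixes the list, so the mismatch lies in the document at hand.

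**Conclusion.** The point holds in a limited form. The allocation text is inconsistent, and the primary model adjusts for two of three allocation factors without giving a reason. Nothing here implies bias or an inflated type I error. In a baseline-adjusted analysis with 35 completers and r between 0.2 and 0.4, the test is at most slightly conservative (about 4.2 to 5.1% across simulations) and about 0 to 5 points of power are lost. In both tabulated simulations power stays above the planned 80% even without BMI. At r = 0 the omission costs nothing. In a complete two-visit mixed model, adding BMI as a main effect alone would gain nothing for the change contrast.

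These sizes rest on an assumed correlation, assumed category cut-points and coin probability, and dropout at random. The severity is minor to moderate: the wording needs correcting, and the analysis change is cheap.

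**What to change.** - **Section 3:** replace the stratification wording, including HbA1c, with the method in 8.2: minimisation in Qminim on age, sex and BMI.
- **Section 8.2:** remove the reference to variable block randomisation so that one procedure remains.
- **Section 10.1:** estimate the treatment effect on week-12 insulin sensitivity adjusted for its baseline value and for age, sex and BMI. This agrees with the 2.70 residual SD in section 4.4. If the two-visit mixed model is kept, name the intervention-by-period term as the contrast and enter each allocation factor with its interaction with period. In that form the gain depends on how well BMI predicts the change, not the level.

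The cost is wording in three sections and, in the baseline-adjusted model, one further degree of freedom for BMI. BMI is already available from screening, so no new data are needed. If BMI proves not to be prognostic, about 1 point of power is lost.

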### **8.3 Study procedures**

Whenever participants are expected to be physically present at our facilities, they will be asked to travel by car or public transport to limit the physical activity prior to the experiments.

Prior to the screening and CIDs, subjects are asked to refrain from alcohol and strenuous physical activity 24h and need to arrive in the morning after a >10h overnight fasting period.

#### **8.3.1 Screening**

After recruitment (see [Chapter 11.2 for additional information](#)), a screening visit will take place. During this visit, the purpose and design of the study will be explained again and in- and exclusion criteria will be discussed, questions will be answered and additional information will be provided if necessary. If the person seems eligible, informed consent must be signed in the presence of the investigator before proceeding. After signing, the participant will be asked to provide an overview of his/her complete medical history and family history of diabetes mellitus, medication and substance use, recent weight changes, and an insight in their usual daily/weekly physical activity and diet. Furthermore, multiple questionnaires (see [8.3.10 Questionnaires](#)) will be filled in, a physical examination will be performed and blood samples will be drawn (see below).

#### **8.3.2 Physical examination**

During the screening, on CID 1+3, in week 2 and 6, a physical examination will be performed, consisting of measurement of blood pressure and anthropometrics (length, weight, waist circumference, waist to hip ratio). Blood pressure will be measured three times; the first measurement will be used to acclimatize the participant to the measuring: data from this measurement will be omitted from analysis. All other body measurement will be taken twice to ensure correct data gathering and reduce variability.

### 8.3.3 Blood samples

During the study period, multiple blood samples will be taken, most of which will be drawn right before or during the hyperinsulinemic-euglycemic clamp. During the screening, fasting glucose, HbA1c, and liver and kidney function will be determined to assess eligibility. Also, on CID 2, CID 4 and in week 6, blood samples will be taken to assess the following elements:

Glucose, insulin, HbA1c, haemoglobin, leucocytes, C-reactive protein (CRP), interleukin 1 (IL-1), IL-2, IL-6, IL-8, IL-12, interferon-gamma (IFN- $\gamma$ ), lipopolysaccharide binding protein (LBP), lipopolysaccharides (LPS), triacylglycerol (TAG), high-density lipoprotein (HDL), low-density lipoprotein (LDL), total cholesterol, glucagon-like peptide 1 (GLP-1), peptide YY (PYY), acetate, propionate, butyrate, valerate, isovalerate, isobutyrate, lactate, free fatty acids (FAA), branched-chain fatty acids (BCFA), leptin, aspartate amino transferase (ASAT), alanine amino transferase (ALAT), creatinine, ureum, zonulin, dopamine, FACS on immune cells.

Specific blood samples will be needed during the hyperinsulinemic-euglycemic clamp.

All samples consist of a maximum of 10ml blood per sample and will be analysed by the laboratories of the MUMC+. The total amount of blood needed is ~380ml (screening 20ml, CID 1+2 165ml (baseline 15ml, clamp 150), week 6 10ml each, CID 3+4 165ml (endpoint 15ml, clamp 150)).

### 8.3.4 Faecal samples

Participants will hand in a faecal sample on CID 2+CID 4 and in week 2 and 6 to determine the amount of faecal saccharolytic and proteolytic fermentation substrates (e.g. SCFA, and BCFA and indoles, respectively), energy content and the composition of the microbiome, using 16S RNA sequencing. A sample container will be provided for every collection.

### 8.3.5 Multisugar test

Gut permeability will be assessed with the Multisugar test (MS), performed by using specific orally administered sugars (1 gram lactulose, 1 gram sucralose, 1 gram erythritol, 0.5 gram rhamnose) which are all either commonly used sugars, European Food Safety Authority-approved artificial sweeteners or found to be safe for administration by previous studies. These sugars will be dissolved in water, ingested, absorbed throughout the gastrointestinal tract and eventually excreted in the urine. Higher urinary sugar concentrations indicate higher gut permeability. This test will be performed on either CID 1+3 or on CID 2+4, depending on logistics. The multisugar test will take place after an overnight fast, on the same CID as the fMRI. Participants will remain fasted for 5 hours after sugar ingestion.

### 8.3.6 Urine samples

Participants will collect 24-hour urine portions after the MS. Urine will be collected in for the first five hours after MS in one container, and from 5-24 hours after sugar ingestion in another. This allows assessment of gut permeability in the small and large intestine, respectively. Additionally, urinary nitrogen concentrations will be analysed to estimate protein oxidation in order to calculate carbohydrate and fat oxidation from the indirect calorimetry measures.

### 8.3.7 Dual-energy X-ray absorptiometry (DEXA) scan

On CID 1 and 3, a DEXA scan (effective radiation dose: ~20 $\mu$ Sv) will be conducted to determine body composition (fat percentage, fat distribution, lean body mass), using facilities at MUMC+ (MUMC+, Discovery A, Hologic). There will be no discomfort of the DEXA scan.

### 8.3.8 Functional Magnetic Resonance Imaging (fMRI)

Apart from a DEXA scan, we will be using functional magnetic resonance imaging (fMRI) on CID 1 and 3 to determine changes in brain activity related to food reward before and after the intervention. A MRI scan is a non-invasive, commonly used radiological diagnostic technique. Apart from a rather narrow space in which the participant needs to be placed and a relatively noisy procedure, no discomfort will be present. In case of claustrophobia, this part might have to be omitted from the testing procedure or an eligible participant will not be included in the trial. Furthermore, hearing protection might be offered in necessary. In case of any fMRI-exclusion criteria are met (see [chapter 4.3.1](#)), the MRI will not take place.

Scanning will be performed on a 3T MRI scanner at the facilities of Scannexus. The scan will take place after an overnight fast. During scanning, images of different types of food and non-food will be displayed. A total set of 120 images will be used during the scan and will be presented in 12 blocks of 10 images for 2 seconds per image. Participants will be instructed to think about how much they like each shown subject. Between each block, there will be a 10 second break during which a fixation cross will be shown, as well as questions ensure participants maintain focused on the task. Images will consist of high-calorie foods (Fries, donuts, hamburgers etc) and low-calorie foods (vegetables, fruits etc). All images will be retrieved from a verified database.(41-44)

